## 3.3 Additional measures in the intervention group

Adherence to the intervention will be calculated using records kept by staff, usage diaries kept by participants and data available from the devices themselves. In addition, the treating physiotherapist will estimate a global level of adherence (in five categories: 0%, <25%, 25–49%, 50–74% and ≥75%) during the 6-month intervention.

**Usability,** the impression of usability of different technologies will be measured using the System Usability Scale (SUS)^14,15^ assessed at 3 weeks, 12 weeks and 6 months. The SUS is a 10-item scale in which each item is scored between 1 (strongly disagree) and 5 (strongly agree). Items were a mix of positive and negative statements. To adjust for this, items 1,3,5,7 and 9 score contribution is the scale score minus 1 and for items 2,4,6,8 and 10 the score contribution is 5 minus the scale score. The total score is the sum of the adjusted item scores multiplied by 2.5 and ranges from 0 to 100, with a higher score indicating greater usability.

**Enjoyment,** the impression of enjoyment using different technologies will be assessed with the Physical Activity Enjoyment Scale (PACES)^16^ assessed at 3 weeks, 12 weeks and 6 months. The PACES is an 18-item scale in which each item is scored between 1 and 7. Item scores are reversed for questions that give a lower score for a positive comment e.g. 1=I enjoy it and 7=I hate it. The following questions have their scores reversed: questions 1,4, 5,7,9,10,11,13,14,16,17. The total score is the sum of the 18 items and ranges from 18 to 126, with a higher score indicating greater enjoyment.

# **4. STATISTICAL ANALYSIS**

Between-group comparisons for each of the continuously scored outcome measures will be made using linear models with baseline scores entered as a covariate. Fall rates between groups will be compared using negative binomial regression. Interaction terms will be used in the models to assess whether effects of the intervention differed according to age or a neurological versus non-neurological cause of the mobility limitation. Primary analyses will be pre-planned, conducted while masked to group allocation and use an intention-to-treat approach. All analyses will be overseen by the study statistician (SH).

## 4.1 Analysis principles

• Data will be coded to permit blinding to group allocation in the analysis of primary outcomes.

• The primary analyses will be conducted in accordance with the intention-to-treat principle.

• All tests are two-sided and the nominal level of α will be 5%.

• All statistical analyses will be adjusted for baseline scores for that variable (except WHODAS and IPEQ for which baseline scores were not measured) but no other variables except where indicated. Sensitivity analysis will be conducted not adjusting for baseline scores for the coprimary outcomes only.

• Subgroup analyses will be pre-specified and outlined below. These will be carried out irrespective of whether there is a significant treatment effect on the primary outcome.

• Where data are missing due to loss to follow up, we will report the number of observations; we will not impute missing values for the primary analyses. Sensitivity analysis may be conducted for the primary outcomes using multiple imputation of missing data if more than 10% of outcome data are missing.

• P-values will not be adjusted for multiplicity. A significant effect must be observed on both co-primary endpoints to declare the intervention effective. However, the outcomes and time points are clearly categorised by degree of importance (primary and secondary) and a limited number of subgroup analyses will be pre-specified.

• Descriptive statistics will include numbers and percentages of participants with specific scores or means and standard deviations in each group at baseline and follow-up.

##

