**Activity and participation**, the WHO Disability Assessment Schedule 2.0 (WHODAS 2.0)^6^, a 12-item self-report measure of activity performance and participation covering 6 domains, will be completed at 3 weeks, 12 weeks and 6 months. The scores assigned to each of the 12 items – “none” (1), “mild” (2) “moderate” (3), “severe” (4) and “extreme” (5) – are summed to give a score ranging from 12 to 60, where 12 = no disability and 60 = full disability.

**Physical activity**, the 10-item Incidental and Planned Exercise Questionnaire^7^ assesses the level of physical activity relating to both basic and more demanding activities at 3 weeks, 12 weeks and 6 months. The total time spent doing activities is summed across all components and expressed as hours per week. The score is derived from multiplying frequency score and duration score (see Appendix 4) to create a total duration for the week score: Total activity score = (Q1*Q2) + (Q3*Q4) + (Q5*Q6) + (Q7*Q8) + (Q9*7) + (Q10*7), with a higher score indicating a higher physical activity level. Subscale scores will also be calculated for home exercise (Q2) and walking activity (Q5*Q6)+(Q6*Q7).

**Fall-related confidence** will be assessed with the Activities-Specific Balance Confidence Scale^8^ at 3 weeks, 12weeks and 6 months. This is a 16-item scale with each item scored between 0 to 100 with 0 representing no confidence and 100 representing complete confidence. The 16 items are summed together and then divided by 16 (the number of items) to give a total score between 0 and 100 with a higher score indicating a higher confidence in balance.

**Cognition**, will be assessed using the Trail Making Test parts A and B^9^ at 3 weeks and 6 months. Trails Part A measures processing speed and involves participants connecting consecutive numbers (e.g., 1-2-3). Part B is a measure of executive function of ‘task shifting’ and involves participants connecting alternating letters and numbers (e.g.,1-A-2-B). The difference in time between the two parts (B minus A) will be calculated to isolate the executive component of this test with a lower time reflecting better executive function.^10^ Trails Part A score and Trails Part B scores will also be calculated.

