## 4.5 Secondary outcomes

Physical Activity:

- The effect of group allocation on the continuous variable time spent upright (minutes per day averaged over days worn), assessed using the activPAL activity monitor at 3 week follow-up will be analysed using linear regression models with baseline scores entered into the linear regression models as covariates.
- The effect of group allocation on the continuous variable ‘average number of steps per day’ assessed using the activPAL activity monitor at 3 weeks and 6 months follow-up will be analysed using linear regression models with baseline scores entered into the linear regression models as covariates.
- average number of transitions per day’ at 3 weeks and 6 months follow-up will be analysed using linear regression models with baseline scores entered into the linear regression models as covariates.

Mobility:

- For this continuous secondary outcome, the groups will be compared on 3 week assessment CSPS, adjusted for baseline scores.
- A secondary analyses will be conducted using the 12-point scored version of the Short Physical Performance Battery^2^ and the sub-scores for the three test items: standing time with the feet in different positions (together, side by side, semi-tandem, tandem and single leg stance) (0-4), 4-metre walk (0-4), and repeated chair stand test (0-4). For these outcomes, the groups will be compared at 3 weeks and 6 months, adjusted for baseline scores.

For the other continuous secondary outcomes (see Appendix 1), the effect of group allocation at the specified time points cognition (3 weeks and 6months after randomisation), self-reported physical activity, activity performance and participation; quality of life, balance confidence and technology self-efficacy (3 and 12 weeks and 6 months after randomisation) will be analysed using linear regression models with baseline scores entered into the linear regression models as covariates. Or if distributions are overly skewed (on visual inspection of histograms) the change scores (post-pre) will be analysed. Mean between-group differences and their 95% CIs will be reported. In addition, self-reported measures of technology usability and enjoyment will be obtained from the intervention group (3 and 12 weeks and 6 months after randomisation).

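### Section 4.5 prescribes baseline adjustment or change scores for WHODAS and IPEQ, which have no baseline: the Section 4.1 exception leaves a valid but unadjusted comparison with no usable fallback for skewness

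*SAP*

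**What the plan says.** Four places in the SAP bear on this.

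- **Section 4** gives the general rule for every continuously scored outcome: "linear models with baseline scores entered as a covariate". It states no exception.
- **Section 4.1** adjusts all analyses for the variable's own baseline, "except WHODAS and IPEQ for which baseline scores were not measured) but no other variables except where indicated".
- **Section 4.5** names, among the remaining continuous secondary outcomes, "self-reported physical activity, activity performance and participation; quality of life, balance confidence and technology self-efficacy". It says that the effect of allocation on these "will be analysed using linear regression models with baseline scores entered into the linear regression models as covariates". It then adds: "Or if distributions are overly skewed (on visual inspection of histograms) the change scores (post-pre) will be analysed". The Section 4.1 exception is not repeated.
- **Section 3.2** identifies the instruments. WHODAS 2.0 is "a 12-item self-report measure of activity performance and participation covering 6 domains, will be completed at 3 weeks, 12 weeks and 6 months", and IPEQ is the physical activity questionnaire, on the same three occasions. Appendix 1 shows the same schedule.

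Two other sections matter for the fallback. Section 4.2 has the blinded inspection of distributions decide whether change scores are used. Section 4.4 provides robust regression as a sensitivity analysis, but only within the mobility primary outcome.

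**The concern.** Section 4.5 offers two methods for WHODAS and IPEQ, a model with a baseline covariate and a post-minus-pre change score. Both need a measurement that Section 4.1 says was not taken. An analyst working from Section 4.5 alone would have no method to apply.

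Two things are at stake. The first is the treatment of skewness. The change score is the only remedy that Section 4.5 offers, so if either outcome is judged overly skewed the method would have to be chosen after the data have been inspected. The histogram review is blinded, but Sections 4 and 4.1 promise masked analysis only for the primary analyses and outcomes. The SAP therefore does not ensure that a substitute method for these two outcomes would be chosen blind.

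The second is efficiency. With no baseline of their own and no other covariate indicated, WHODAS and IPEQ are compared with no adjustment at all, although the trial collects a baseline mobility score and stratifies on two factors that could serve as covariates.

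**Working it through.** **1. Which outcomes are caught.** Section 3.2 ties activity performance and participation to WHODAS and self-reported physical activity to IPEQ. Both constructs appear by name in the Section 4.5 list. Both instruments appear by name in the Section 4.1 exception. The two sections therefore cover the same outcomes.

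**2. What each rule yields for them.**

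| Rule | Needs a baseline? | Computable for WHODAS and IPEQ? |
|---|---|---|
| Sections 4 and 4.5: linear model with baseline covariate | Yes | No |
| Sections 4.2 and 4.5: change score if overly skewed | Yes | No |
| Section 4.1 exception: linear model on arm, no covariates | No | Yes |
| Section 4.4: robust regression; stratification-adjusted model | Robust form does not in itself require one | Stated only for the mobility primary outcome |

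The main model thus resolves to an unadjusted comparison. The skewness fallback does not resolve to anything.

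**3. How many comparisons.** WHODAS total and IPEQ total at three time points each give 3 + 3 = 6. Section 3.2 also says that two IPEQ subscales will be calculated. If these are compared between groups as well, the count is 3 + 3 × 3 = 12. Neither Section 4.5 nor Appendix 1 lists the subscales separately, so 6 is the firm number and 12 the upper one.

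**4. What adjustment for other baseline variables might gain.** The SAP states no sample size, standard deviation or correlation for these outcomes, so there is no figure of its own to reproduce. The following is illustration only. Let r be the correlation between the outcome and a baseline covariate (or the multiple correlation for a set).

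- Residual variance relative to unadjusted: 1 − r²
- Standard error, unadjusted relative to adjusted: 1/√(1 − r²)
- Equivalent gain in sample size: 1/(1 − r²) − 1

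| Assumed r | 1 − r² | Variance cut | SE ratio | Equivalent extra participants |
|---|---|---|---|---|
| 0.2 | 0.96 | 4% | 1.02 | 4% |
| 0.3 | 0.91 | 9% | 1.05 | 10% |
| 0.4 | 0.84 | 16% | 1.09 | 19% |
| 0.5 | 0.75 | 25% | 1.15 | 33% |

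At the low end the gain is slight and at the high end worthwhile. Nothing in the document says where this trial falls.

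**The case against.** The strongest reply is that Section 4.1 sets principles for all analyses and excepts these two instruments by name, with the reason. A specific exception governs a general sentence, and no analyst could enter a baseline that does not exist. This stands for the main model. A reader might infer from Section 4.5 that WHODAS and IPEQ have no executable analysis, but the documents do not support that. The unadjusted linear comparison can be run and is unbiased under randomisation.

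A second reply is that an unmeasured baseline cannot be adjusted for, so any loss of precision exists only against a model that the SAP never promised. The SAP deliberately keeps covariates few: the primary mobility analysis adjusts for baseline score alone and leaves the stratification factors to a secondary analysis. On that view, giving two secondary outcomes more covariates is a change of policy. Part of this stands. A reader might infer that a material loss of precision has been shown. It has not, because the correlations are assumed. The SAP also does not say that baseline CSPS is complete or strongly prognostic for these outcomes, or that IPEQ will be skewed. Nor is function at baseline left wholly to chance, since allocation is stratified by site and neurological condition. The covariate proposal is therefore an improvement available at no cost in data collection, and does not correct an invalid analysis.

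Neither reply repairs the fallback. The Section 4.1 exception concerns adjustment and is silent on skewness, and no other section supplies a method for these outcomes.

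**Conclusion.** The point holds in limited form. Sections 4 and 4.5 conflict with Section 4.1 on WHODAS and IPEQ. The conflict can be resolved for the main model, in favour of a valid but wholly unadjusted comparison. It cannot be resolved for the skewness rule, which for these two outcomes has no computable content. This rests on the text alone and needs no assumption.

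The reach is 6 secondary comparisons, or 12 if the IPEQ subscales are tested. The co-primary analyses, and the rule that both must be significant to declare effectiveness, are untouched. No bias arises. The possible gain in precision depends entirely on the assumed correlation and is offered only as support for the form of the fix. The missing fallback matters only if WHODAS or IPEQ turns out overly skewed. That is plausible for IPEQ, a sum of frequency-by-duration products bounded below at zero, but the SAP shows no distribution for it.

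**What to change.** - In Sections 4 and 4.5, repeat the Section 4.1 exception for WHODAS and IPEQ.
- State their model: linear regression on arm, with site, neurological condition and baseline CSPS as covariates, at each time point. Mark this in Section 4.1 as one of the indicated departures from the rule against other covariates, and say how a missing baseline CSPS would be handled.
- State in Sections 4.2 and 4.5 that no change-score analysis applies to these two outcomes. If they are judged overly skewed at the blinded review, report the same between-group mean difference with robust or bootstrap confidence intervals.
- Say whether the IPEQ subscales are compared between groups under the same model.

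The cost is SAP wording only. The covariates are already in the plan: baseline CSPS enters the primary mobility model, and the two factors define the stratification. No new data, visits or participants are needed.

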## 4.3 Activity (primary outcome)

## The time spent upright (minutes per day averaged over days worn), assessed using the activPAL activity monitor will be treated as a continuous variable. The effect of group allocation on the outcomes at 6-month follow-up will be analysed using linear regression models with baseline scores entered into the linear regression models as covariates. Or if distributions are overly skewed (on visual inspection of histograms) the change scores (post-pre) will be analysed.

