## 4.4 Mobility (primary outcome)

The primary analyses will be conducted using linear models with baseline scores entered as a covariate. The groups will be compared on 6-month assessment scores. The primary analysis will use the CSPS^1^ This is the continuously scored version of the Short Physical Performance Battery^2^ and gives a composite score between 0 and 3 based on timed performance of three mobility tasks: the ability to stand for up to 10 sec with feet in different positions (together, side by side, semi-tandem and tandem), 4-metre walk and time to rise from a chair five times.

The primary analysis will be adjusted only for baseline scores. A secondary adjusted analysis will be conducted adjusting for the stratification factors of study site and health condition (whether or not the person has a neurological condition that affects daily activities). Further adjusted analyses will be conducted if major imbalances between the groups at baseline are observed.

If outliers are present in the data or the model assumptions are grossly violated after treatment is included in the model, some sensitivity analyses based on robust regression will be conducted.

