## 4.6 Sub-group analyses

Subgroup analyses will be undertaken on the primary outcomes i.e., physical activity and mobility. All subgroups will be defined by data collected prior to randomisation. Subgroup analysis will be conducted on each of the primary outcomes for:

- Neurological versus non-neurological condition
- Sex (male versus female)
- Age (age entered as continuous covariate and as categorical (above and below median age); both analyses will be considered)
- Baseline mobility level (analysis with 12-point SPPB as a continuous interaction term with data also presented as a dichotomous term above and below median)
- Technology use prior to hospital admission (used vs. not used a computer, tablet, smartphone, pedometer or gaming console in the month prior to hospitalisation)
- State (NSW versus SA)

Unadjusted *p*-values will be reported and the number of declared subgroup analyses will be specified in all publications. The main analysis for each subgroup will be an interaction test in the linear regression model to determine whether the effect of treatment differs significantly across categories for that particular subgroup. The between-group differences within each of the subgroups will be reported, as well as the *p*-value for the interaction test.

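### The two co-primary models adjust only for the outcome's own baseline score; pre-specifying age, and baseline mobility for upright time, could add modest precision at almost no cost

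*SAP*

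**What the plan says.** SAP section 4.1 sets the general rule: analyses adjust for the baseline score of the variable concerned "but no other variables except where indicated".

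- **Upright time (section 4.3).** The 6-month comparison uses "linear regression models with baseline scores entered into the linear regression models as covariates". No other covariate is named.
- **Mobility (section 4.4).** The text is explicit: "The primary analysis will be adjusted only for baseline scores". A secondary analysis then adds study site and neurological condition, and further adjusted analyses follow if major baseline imbalances are seen.
- **Subgroups (section 4.6).** Age, as a continuous variable, and baseline mobility, as the 12-point SPPB, enter interaction models for both co-primary outcomes. On timing, the section says: "All subgroups will be defined by data collected prior to randomisation".
- **Success rule (section 4.1).** "A significant effect must be observed on both co-primary endpoints to declare the intervention effective". Tests are two-sided at 5%.

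**The concern.** In a randomised comparison with a linear model, a pre-randomisation covariate that predicts the outcome reduces the residual variance. It does so without changing the mean difference being estimated and without biasing it. The trial holds two such candidates, age and baseline mobility, and plans to use them only in subgroup models.

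For upright time both would be new to the model. A person's measured mobility and age may well say something about activity six months later that baseline upright time does not. For the CSPS, baseline mobility is already in the model as the outcome's own baseline, so only age would be new.

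What is at stake is precision. The intervention is declared effective only if both tests succeed, so avoidable imprecision on upright time also lowers the chance of overall success.

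**Working it through.** **Which exceptions reach the primary tests?** The clause in section 4.1 leaves room for other covariates, so each place where they appear has to be checked.

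- The analysis in section 4.4 with site and neurological condition is labelled secondary and is written only under mobility.
- The imbalance-triggered analyses in section 4.4 are additional to the primary analysis.
- The models with age and SPPB in section 4.6 are subgroup interaction tests.

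None of these changes the primary model for either endpoint.

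**Are the covariates available?** Yes. Section 4.6 uses age and baseline SPPB as pre-randomisation data. Section 4.4 uses baseline CSPS as a covariate.

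**Inputs for the size.** The SAP states no sample size, power, standard deviation or correlation, so there is no figure of its own to reproduce.

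- From the SAP: two-sided α = 0.05 for each test, and both tests must be significant.
- Assumed: 80% power on each endpoint under the planned model.
- Assumed: q, the share of the residual variance of 6-month upright time (after baseline upright time) explained by age and baseline CSPS, runs from 0 to 0.20.
- Assumed: mobility power stays at 80%, that is, age adds nothing there. Any contribution from age would raise the joint figures somewhat.

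**Formulas.** The noncentrality for 80% power is 1.960 + 0.842 = 2.802. With the covariates, power = Φ(2.802/√(1−q) − 1.960). The equivalent increase in sample size is 1/(1−q) − 1. Joint power for independent tests is the upright-time power × 0.80.

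At q = 0.05: 2.802/√0.95 = 2.875; 2.875 − 1.960 = 0.915; Φ(0.915) = 0.820; joint 0.820 × 0.80 = 0.656.

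| q | Equivalent N | Power, upright time | Joint, independent | Joint, correlation 0.5 |
|---|---|---|---|---|
| 0 | +0% | 80.0% | 64.0% | 68.7% |
| 0.01 | +1.0% | 80.4% | 64.3% | 69.0% |
| 0.02 | +2.0% | 80.8% | 64.6% | 69.3% |
| 0.05 | +5.3% | 82.0% | 65.6% | 70.1% |
| 0.10 | +11.1% | 84.0% | 67.2% | 71.4% |
| 0.20 | +25.0% | 87.9% | 70.4% | 73.9% |

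The last column uses a bivariate normal distribution for the two test statistics.

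Starting from 90% on each endpoint, q = 0.05 gives 91.4% on upright time (joint, independent: 81.0% to 82.3%) and q = 0.10 gives 92.7% (joint 81.0% to 83.5%).

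**Is that range of q reasonable?** For baseline mobility alone, q = (r_ym − r_yb·r_bm)² / [(1 − r_yb²)(1 − r_bm²)], where y is 6-month upright time, b its baseline and m baseline mobility. Assumed correlations: r_yb 0.4 to 0.7, r_ym 0.3 to 0.5, r_bm 0.3 to 0.6.

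- Lowest: r_yb = 0.5, r_ym = 0.3, r_bm = 0.6 gives a numerator of (0.3 − 0.30)² = 0, so q = 0.
- Middle of the grid: 0.4, 0.4, 0.6 gives 0.16²/(0.84 × 0.64) = 0.0256/0.5376 = 0.048.
- Highest: 0.4, 0.5, 0.3 gives 0.38²/(0.84 × 0.91) = 0.1444/0.7644 = 0.189.

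So q may be close to zero, and a middling value is about 0.05. From an 80% base, that is about 2 points on upright time and 1.5 points jointly.

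**The case against.** The strongest reply is that nothing here is wrong. Adjusting for the outcome's own baseline is valid, pre-specified and clear, and a longer covariate list is a matter of preference whose benefit cannot be sized from the SAP. The first half of this stands in full: the planned tests are unbiased and hold their level. The second half stands as to size, since q is assumed and may be near zero. It does not remove the point, because the change needs no new data and very few degrees of freedom.

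A reader might also infer four stronger things that the SAP does not support.

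- **Section 4.1 forbids all other covariates.** It does not. The exception clause is there and is used in section 4.4, and other variables enter the models in section 4.6, though never in the primary tests.
- **Both endpoints gain equally, so the improved power can be squared.** At q = 0.20 that would give 0.879² = 77%. Baseline CSPS is already in the CSPS model, so the gain from adding mobility falls on upright time alone. With mobility held at 80%, the figure is 70%.
- **Baseline upright time is a poor covariate because the ward restricts activity.** The SAP says that participants are rehabilitation inpatients. It says nothing on how well baseline upright time predicts the 6-month value.
- **Listing age and mobility as subgroup factors shows that they are prognostic.** Effect modification and prognosis are different properties, and section 4.6 lists sex, state and prior technology use as well.

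**Conclusion.** The point holds as a modest, low-cost efficiency improvement, mainly for upright time. The primary models leave out two pre-randomisation variables that the trial holds and that plausibly carry information on 6-month upright time beyond its own baseline.

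The benefit ranges from nothing to about 8 points of power on that endpoint, and from nothing to about 6 points jointly under independence. A middling expectation is near the bottom of both ranges. These figures depend on the assumed 80% starting power, the assumed q and mobility power held constant. Positive correlation between the two tests makes the joint gain slightly smaller. They apply to the baseline-adjusted model and not to the change-score alternative that section 4.3 allows for skewed data.

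The planned analysis is neither biased nor internally contradictory on this point. A trial analysed as written would still give a valid result.

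**What to change.** Before unmasking, amend three sections:

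- **Sections 4.1 and 4.3:** the primary upright-time model includes baseline upright time, baseline CSPS and age as a continuous variable.
- **Section 4.4:** the primary CSPS model includes baseline CSPS and age as a continuous variable.
- **Section 4.1:** the own-baseline-only model is kept as a sensitivity analysis for each co-primary outcome.

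Add a rule, fixed in advance and applied without regard to group, for participants with a missing baseline CSPS. Otherwise the extra covariate could remove people from the upright-time analysis and offset the gain.

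The cost is SAP wording, two degrees of freedom for upright time and one for CSPS. No new data are needed.
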